##### Parent/carer telephone/Skype interviews

Interim findings from the workshop will be used to inform and develop the telephone/Skype interview topic guide as part of an iterative (reflective) approach to the research, although the key topics and structure are likely to be similar to those of the workshop focus group topic guide.

Recruitment to telephone/Skype interviews will take place at all seven study sites. If a parent/carer is recruited prospectively, then written informed consent will be obtained at the site. Parents/carers identified retrospectively who contact the study team will be included on a register with their contact details. Approximately one week prior to the interview, all parents/carers will be sent a copy of the information sheet, consent form, list of outcomes previously developed for use in the parent workshop and copies of the NOVEMBR study (draft) participant information sheet to consider. Parents/carers will be contacted by the research team to ascertain whether they still wish to participate in the interview, to allow them to ask questions and to arrange a convenient date and time for the interview. Parents/carers will be able to select whether they would prefer a telephone or Skype interview.

The researcher will begin the call by explaining the aims of the study and provide further opportunity to ask questions. Parents/carers will be advised that they are free to withdraw from the study at any point without giving reason. They will also be asked for permission to use any data already collected. Data may include age, gender, risk factors, severity of illness and the first part of the postcode of the family home. Parents/carers, irrespective of being recruited prospectively or retrospectively, will be guided through the consent form and verbal consent will be obtained. This verbal consent process will be digitally audio recorded and saved on a separate file from the interview recording.

Interviews will be conducted with up to 15 parents/carers based on similar studies [59] or until data saturation is achieved (i.e. when no more new themes are identified). All interviews will be conversational and participant-centred to ensure that the interview content reflects their own priorities and views on the proposed trial design. It is anticipated that interviews will take no longer than 60 min. To identify important outcomes, parents/carers will be asked about their experience of having a child with bronchiolitis and then be requested to look at the outcome list. The researcher will go through each outcome on the list to check understanding and provide an explanation if required. Parents/carers will be asked to identify which outcomes on the list are important to them. Using a prioritisation grid, parents/carers will be asked to rank the preidentified outcomes in order of importance. Finally, parents/carers will be asked to comment on the draft participant information sheet for a potential future clinical trial.

##### HCP focus group workshops

Recruitment of HCPs will take place at all seven study sites. Information and invitation to participate in the study will be disseminated via health professional organisation global mailing lists or through a brief presentation at appropriate clinical team meetings. Clinical leads will be contacted to suggest an HCP who may fit the inclusion criteria. An HCP may also be approached directly by a member of the research team and invited to participate. In addition, HCPs who participated in two recent National Institute for Health Research (NIHR)-funded bronchiolitis studies (UKCRN 10194 and UKCRN 10755) will be re-approached by email. HCPs will be invited to contact the research team to register an interest to take part in one of three workshops situated at different geographical locations around England. The HCP will be asked to provide the following information: contact details; profession type; grade; clinical location; geographical area. A list of those HCPs who register an interest in taking part in the study will be used to purposively sample by profession, grade, clinical speciality, hospital setting (secondary or tertiary) and geographical location. A member of the research team will contact those HCPs who have been selected to explain key aspects of the study information, including the purpose of the study, what is involved and the risks and benefits of participation. Care will be taken to ensure that HCPs do not feel coerced to participate in the study, and they will be advised that they can withdraw from the study at any point without giving reason. If an HCP withdraws, permission will be sought from the HCP to use any data already collected.

As with the parent/carer workshop, there will be three focus groups (outcomes; study design; consent) within the workshop, each lasting approximately an hour. The research team will use a workshop topic guide, similar to the one used with the parents/carers, to explore identification and prioritisation of outcomes; consent (including decision-making in the emergency setting) [58]; length and content of the participant information sheets; and acceptability of the proposed trial (including identification of potential barriers for participation). Written informed consent will be obtained at the beginning of the workshop from each HCP participant by either a member of the research team or personnel included on the delegation log.

In the first focus group the list of outcomes and definitions prepared for the parent/carer focus group will be provided for use. HCPs will be asked to reflect upon their experience of managing children with bronchiolitis to identify additional outcomes. All identified outcomes will be recorded on flip-charts. The group will discuss each outcome to clarify meaning, and similar outcomes identified from the workshop discussions may be merged. All additional outcomes identified that are not already on the prepared list will be included for prioritisation. Using TurningPoint software, HCPs will be asked to prioritise outcomes using a Likert scale (1, Extremely important, to 5, Completely unimportant). Those outcomes which were considered either extremely important or important will be recorded on Post-it Notes and included in a prioritisation exercise in focus group two.

Two different study design options will be discussed and explored in focus group two: HFNC compared with standard care and HFNC compared with nCPAP. HCPs will be asked to consider and discuss topic areas related to the design of the clinical trial, such as study interventions and acceptability of a clinical trial of non-invasive ventilation. HCPs will be asked which of the two trial designs should be prioritised. Using a prioritisation grid [57] and the outcomes recorded on Post-it Notes from focus group one; HCPs will be asked to prioritise nine outcomes, including a primary outcome. Similar to the parent/carer focus group, HCPs will be consulted on what should be considered as the minimally important difference for the primary outcome. In the third focus group HCPs will be asked to consider the use of prospective consent and research without prior consent [58] in relation to the two study designs previously discussed. HCPs will be provided with a draft participant information sheet for research without prior consent for consideration.

##### Qualitative data analysis and storage

All focus groups and interviews will be audio recorded and transcribed verbatim by an external transcription company. Transcripts will be pseudo-anonymised. Audio files will be deleted once transcribed; with the exception of the audio recorded consent for parent/carer interviews. All study data will be stored according to data protection requirements and local data governance policies. Identifiable participant data will be kept in a file separate from the anonymised participant data on a secure server on a password protected NHS computer. All identifying details such as names, dates of births and hospitals will be removed and replaced with pseudonyms. All participants will be identified with a unique identifier. All recordings, transcripts and documents will be coded with the unique participant identifier to ensure anonymity. Electronic versions of the transcripts will be stored on the main server of a password protected computer.

Digital audio recordings of focus groups and interviews will be transcribed verbatim. Other data sources derived from focus groups and interviews will include lists of words and phrases written down by the participants and words and phrases recorded on flip charts; field notes made by the researchers will also be analysed. Transcripts and all other data sources will be examined iteratively several times over the course of the analysis. Synthesis of all types of data sources will be undertaken using a constant comparative method [60]. Initial examination of the data will aim to provide an overview of the data with general impressions recorded, including key ideas, themes and concepts arising from the content. A descriptive thematic analysis will then be undertaken [61]. This process will involve manually coding the raw data, then collapsing the coded data under broader themes. Codes and themes will be inductively derived from the data. As new codes emerge, they will be applied iteratively to the whole data set in subsequent examinations of the data sources until no new codes or themes are identified. A descriptive account will be produced for each theme. Finally, outcomes identified from transcripts and other data sources will be grouped under appropriate domains and sub-domains using the predefined conceptual bronchiolitis conceptual framework. QRS NVivo (version 10) software will be used to support the coding and synthesis of data. Field notes will be used to support the analysis through describing the environmental geography, participant interaction, group dynamics, behaviour and non-verbal communication. Field notes will also enable the researcher to reflect on the focus groups and interviews and record any meaningful thoughts and insights.

#### Delphi survey to prioritise outcomes to include in a COS

In the third and final stage, we will undertake a Delphi survey to reach consensus over which outcome measures to include in a COS for trials in the management of children with bronchiolitis. We will adopt this approach to ensure the anonymous opinions of important stakeholders (parents/carers and HCPs) are obtained in a way that gives equal influence to all who participate, and avoids an individual participant being overtly influenced by the opinions of other participants [62, 63].

We will review all outcomes identified from the systematic review and stakeholder consultation (workshops and interviews) for inclusion in the Delphi survey. Outcomes considered similar (for example, those that measure the same phenomenon) will be collapsed and merged. Each outcome will be categorised under the relevant domains and sub-domains in the outcomes framework defined a priori, as previously stated.

Stakeholders who meet the following eligibility criteria will be invited to complete the Delphi survey:Parents/carers of a child hospitalised between 2016 and 2018 (including ED attenders), aged 0–24 months, with a clinical diagnosis of bronchiolitis defined as per NICE Bronchiolitis Guidelines [56]HCPs (nurses, doctors, physiotherapists) who have at least 6- months experience in managing children diagnosed with bronchiolitis.

We will also invite eligible stakeholders who have been involved with earlier phases of the study to participate. Parents/carers who do not speak English or whose child has died during hospital admission will be excluded.

##### Sample and setting

There is currently no standard method to determine sample size for the Delphi survey. A pragmatic decision to recruit up to 40 parents and up to 300 HCPs was taken based on other studies [64, 65]. Efforts will be taken to maximise the response rate across centres and stakeholder groups.

Eligible parents/carers who were approached to participate in workshops or interviews will be asked to complete a permission to contact form. This form will include a box to be ticked to indicate interest in participation in the Delphi survey. In addition, we will invite several UK hospitals to become participant identification centres (PICs). A member of the research team at each PIC will identify eligible parents and provide them with the Delphi information sheet. The information sheet outlines the Delphi survey process and provides instructions on how to contact a member of the study team for more information. PICs will also be asked to display posters advertising the Delphi survey in relevant clinical areas. We intend to make links with a number of general or respiratory-specific patient advocacy groups in order to circulate the poster and the contact details for the research team.

To identify eligible HCPs, the study team will send an email advertising the Delphi survey to professional organisations for them to distribute to members via global email address lists or associated social media sites. Professional organisations will at least include the following: NIHR Clinical Research Network: Children; General and Adolescent Paediatric Research Collaborative - UK and Ireland (GAPR-UKI); Acute Paediatric Emergency Medicine (APEM); Royal College of Nursing Children’s and Young Persons Forum. We will ask PICs to circulate Delphi survey information to the relevant HCPs within their organisation. In addition, clinicians who complete the national survey of current practice will be asked to provide their email address if they wish to be contacted regarding participation in the Delphi survey.

All participants will be invited to pass on details of the study to any of their own contacts who meet eligibility requirements. Potential participants will be given details of how to register when they contact the study team. Screening questions will be included on the Delphi registration page for potential participants to complete. If they do not meet these criteria, then they will be unable to complete the registration process. Eligible participants will be included on a register and allocated a unique identifier. We will use the unique identifier to anonymise and store data and to track attrition rates between rounds. The following information will be collected for each stakeholder group:Parents/carers: When the respondent’s child was hospitalised with a diagnosis of bronchiolitisHCPs: Respondent’s clinical role; whether respondent works in a secondary care, tertiary care or ‘other’ setting; name of respondent’s employing organisation; number of years post-professional registration; grade.

A statement will be included on the Delphi registration page highlighting that completion of the questionnaire will be regarded as consent.

##### Delphi survey methods

We will upload outcomes identified from the systematic review and stakeholder consultation onto the web-based Delphi system (Delphi Manager Application version 1.1). This system will facilitate management of the Delphi survey. A hyperlink to access the survey will be embedded in an email along with the study information sheet. The information sheet will provide participants information on the NOVEMBR study and the Delphi survey, notify participants that their participation is voluntary and stress the importance of completing all Delphi survey rounds. Furthermore, we will inform participants that if they complete all Delphi survey rounds they will be entered into a prize draw to win an iPad and that HCPs will receive a certificate of completion. The Delphi survey will be pilot tested prior to distribution to determine any technical issues with the software, clarity of wording, time taken to complete the survey and ease of use, and the survey will be refined as necessary. We will ask participants to complete each round of the Delphi survey within four weeks following receipt of the email. Participants will be reminded of this at the start of each survey. A reminder email will be sent out at the end of the first week to prompt completion of the survey. Withdrawals will be classed as those participants who contact the NOVEMBR study team directly or write a comment in the survey comments box to indicate they do not wish to participate in any more Delphi survey rounds.

Delphi survey round one will contain:A list of outcomes to be scored, ordered alphabetically by domains. The list of outcomes will include the option to display a more detailed plain language description. The text will be reviewed by the study team and parent representative.An option for a participant to add any additional outcomes and to provide a score for each outcome added.

At the beginning of the survey, participants will be asked the following key question:

*What outcomes are most important in the management of children with bronchiolitis?*

Participants will be asked to score each of the outcomes listed using the Grading of Recommendations, Assessment, Development and Evaluation (GRADE) scale of 1–9 [66]. In the Delphi exercise the scale will be presented in the format 1–9 with 1–3 labelled as 'not important', 4–6 labelled as 'important but not critical', 7–9 labelled as 'critical' and the choice 'unable to score' [66]. Participants will be provided with an option to add additional outcomes that they think are relevant together with a score for each outcome added. Outcomes will be listed alphabetically to avoid potential weighting caused by the order in which they are displayed. Additional outcomes listed by participants will be reviewed and coded by members of the study team to ensure they represent new outcomes. The SMG will be consulted if there is uncertainty. For each outcome, the number of participants who have scored the outcome and the distribution of scores (as a percentage of those who have scored each outcome) will be summarised based on stakeholder group. All outcomes will be carried forward to round two.

The number of participants in each stakeholder group who respond to round one will be assessed following round one closure. Results will be presented as:Total number of registrationsBreakdown of respondents who have completed the survey and their inclusion in the initial email invitationTotal number of respondents who completed the roundTotal number of respondents in each stakeholder groupPercentage of respondents compared to potential respondents as identified from the information provided by clinical leadsPercentage of respondents from other sources (not included in original email invitation)

If a low number of responders (less than 10) is observed for one or more stakeholder groups, the Delphi protocol for future rounds will be reviewed and revised. Where there is only one stakeholder group with a small number of respondents (potentially due to the sample available from clinical teams), then consideration will be given to grouping with another stakeholder group; e.g. physiotherapists may be grouped along with nursing staff. This will be done in consultation with the SMG to ensure appropriateness of grouping. The proposed approach assumes sufficient numbers of stakeholders from each group who respond. Continuation to round two will be considered based on the response to round one. Those who have not taken part in round one and not provided a score will not be invited to participate in round two.

In round two, participants will be shown their own scores for each outcome as well as the scores given by each stakeholder group using a bar chart displaying the distribution of scores. Participants will then be asked to re-score all outcomes and state whether they should be included in a COS. Participants will be provided with the option to explain any significant score changes. Round two will be presented online. The total number of participants invited to take part in round two will be recorded. For each outcome, the number of participants who have scored the outcome and the distribution of scores will be summarised together with the number of participants who have scored the outcome in all rounds. Results of the stakeholder group response will be compared to the whole group response, and the percentage agreement used to determine the structure and focus of the final consensus meeting. Each outcome will be classified as either ‘consensus in’, ‘consensus out’ or ‘no consensus’ as described in Table 1 [66].

**Table 1 Tab1:** Consensus classification for all stakeholder groups

Consensus classification	Description	Definition
Consensus in	Consensus that outcome should be included in the core outcome set	70% or more participants scoring as 7–9 AND < 15% participants scoring as 1–3 in each group
Consensus out	Consensus that outcome should not be included in the core outcomes set	< = 50% of participants scoring as 7-9 in each group
No consensus	Uncertainty about importance of outcome	Anything else

For consensus to have been reached that an outcome should be included in the COS, there must be agreement by a clear majority on the importance of the outcome with only a small minority considering it to be not important at all. For consensus to have been reached that an outcome should not be in the COS, there must be agreement by a clear majority on the lack of importance of the outcome with only a small minority considering it to be important. Whilst the choice of thresholds is inevitably somewhat subjective, the definition of consensus a priori should reduce the chance of consensus being defined post hoc in such a way as to bias the results towards the beliefs of the research team [48]. Once the final analysis of the online Delphi survey has been conducted, the results will be summarised, a report will be written by the study researcher and recommendations for future research will be made based on the findings of the study.

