### Core outcome set (COS) scope and development

The scope of the COS will principally be developed for use in RCTs of interventions (pharmacological or non-pharmacological) for children with a clinical diagnosis of bronchiolitis in a hospital setting. Methods recommended by Core Outcome Measures in Effectiveness Trials (COMET) and COnsensus-based Standards for the selection of health Measurement INstruments (COSMIN) will be used to guide the development of the bronchiolitis COS [48, 51, 52]. A list of outcomes will initially be created from the systematic review and stakeholder consultation (workshops and interviews). Similar outcomes will be collapsed and merged. A conceptual outcomes framework has been developed based on previous exploratory work^1^ (unpublished data) [48, 53]. The outcome domains and sub-domains for the framework will be defined a priori. We will categorise the list of outcomes under relevant domains and sub-domains in the outcome framework prior to inclusion in the Delphi survey. Obtaining consensus for importance for identified outcomes will be an iterative process. A variety of consensus methods will be used within the stakeholder workshops, interviews and Delphi survey, culminating in an end-of-study consensus meeting.

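### Under the stated Delphi rules, an outcome added in round one would return in round two with charts of its proposers' scores only, and be classified after a single panel-wide scoring

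*Protocol article*

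**What the plan says.** The sequence is set out in the Protocol article under Delphi survey methods.

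- **Round one, additions.** Participants score the listed outcomes on the 1–9 scale and may write in others: "Participants will be provided with an option to add additional outcomes that they think are relevant together with a score for each outcome added".
- **Between rounds.** "Additional outcomes listed by participants will be reviewed and coded by members of the study team to ensure they represent new outcomes". The stated purpose of this review is to confirm novelty.
- **Round-one summary.** For each outcome, "the distribution of scores (as a percentage of those who have scored each outcome) will be summarised based on stakeholder group".
- **Carry-forward.** "All outcomes will be carried forward to round two".
- **Round two, feedback.** Here "participants will be shown their own scores for each outcome as well as the scores given by each stakeholder group using a bar chart". Participants then re-score every outcome and say whether it belongs in the core outcome set.
- **Classification.** Each outcome is put into a Table 1 class. 'Consensus in' needs at least 70% scoring 7–9 and under 15% scoring 1–3 in each group. 'Consensus out' needs 50% or fewer scoring 7–9 in each group. Anything else is 'no consensus'.

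No separate display or classification rule is given for added outcomes. Only two rounds are described before the consensus meeting, whose list of outcomes and methods are still to be decided.

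**The concern.** Feedback between Delphi rounds is meant to show each participant where the whole panel stands. For a listed outcome the round-one chart does that. For an added outcome, the only people with a round-one score are those who thought it worth adding. A chart of their scores is a self-selected sample, likely to sit at the top of the scale, yet it would appear in the same format as a chart based on a full stakeholder group.

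The second difficulty is the number of scorings. Non-proposers have no previous score for an added outcome, so round two is their first look at it. Table 1 then treats that first look like the second, informed score given to a listed outcome.

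What is at stake is the class given to outcomes near a Table 1 threshold, and whether readers of the final set can tell which outcomes had the full two-round process. The Delphi section says the method was chosen to give every participant equal influence and to limit sway by other individuals. A chart built from one or a few proposers fits poorly with that aim.

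**Working it through.** The document gives no figure for this point, so there is nothing to reproduce. The check follows one added outcome through the stated steps and then looks at sensitivity near the threshold.

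**Step 1: who has scored it after round one.** The proposer gives a score on adding the outcome. The team then reviews and codes it; no panel-wide scoring is described before round two. The scorers are therefore its proposers, k people.

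**Step 2: what the chart would show.** Percentages are taken over those who scored the outcome, by group. With one proposer who scores 7–9, that group's chart reads 1/1 = 100% critical and every other group's chart is empty.

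**Step 3: share of the panel behind the chart.** The Sample and setting section allows up to 40 parents and up to 300 healthcare professionals, so the maximum panel is 40 + 300 = 340. The share is k/340; the values of k are assumptions.

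| Proposers (assumed) | Share of maximum panel |
|---|---|
| 1 | 1/340 = 0.29% |
| 3 | 3/340 = 0.88% |
| 10 | 10/340 = 2.94% |

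**Step 4: scorings before classification.** Listed outcome: round one plus round two, so two. Added outcome: round two only, so one.

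**Step 5: how much a shift could matter (illustration only).** Assume full recruitment, one healthcare-professional group, independent raters, the same true share p scoring 7–9 in both groups, and only the 70% criterion. The thresholds are 0.70 × 40 = 28 parents and 0.70 × 300 = 210 professionals. The chance of passing is P(X ≥ 28), X ~ Bin(40, p), times P(Y ≥ 210), Y ~ Bin(300, p).

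| p | Parents | Professionals | Both |
|---|---|---|---|
| 0.65 | 0.314 | 0.038 | 0.012 |
| 0.70 | 0.577 | 0.528 | 0.305 |
| 0.75 | 0.821 | 0.979 | 0.804 |

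For a borderline outcome, moving p from 0.70 to 0.75 takes the chance of passing from 0.305 to 0.804. This shows that modest sway could change a class. It does not show that such sway would occur; the document gives no basis for its size.

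**The case against.** The strongest reply is that the skewed chart is inferred. No sentence says that a write-in score will be displayed as a group distribution. Display is partly a matter for the survey software, which is to be piloted and refined, and the full protocol and the flow diagram are not shown. The text also speaks of all rounds and future rounds. This limits how firmly the point can be put. But the article does state a feedback rule for each outcome and a carry-forward rule for all outcomes, without exception, and it describes only two rounds. Followed literally, those rules give the result above.

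Three stronger readings are tempting and are not supported:

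- **That added outcomes are judged on their proposers' scores.** They are not. Table 1 follows round two, when the whole responding panel scores the outcome.
- **That additions are the parents' main means of correcting a list drawn from published trials.** Up to 20 parents in workshops, up to 15 in interviews and about 80 healthcare professionals feed the list beforehand, and outcomes they name that are missing from the prepared workshop list are added to it for prioritisation.
- **That added outcomes would be wrongly discarded.** 'Consensus out' requires 50% or fewer scoring 7–9 in every group, so support from more than half of one group prevents it. A consensus meeting with discussion and a vote follows, and nothing bars an outcome from it. Nor is an outcome classed 'out' guaranteed a place, since the list is undecided.

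It might also be said that the plan breaks its own promise: "Obtaining consensus for importance for identified outcomes will be an iterative process". That sentence introduces a process spanning workshops, interviews, Delphi and the meeting. It does not promise every outcome two Delphi scorings, so there is no direct contradiction.

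**Conclusion.** The point holds as a gap in the stated procedure. Applied as written, the feedback rule gives added outcomes charts made up only of their proposers' scores, and the classification rule gives them a Table 1 class after one panel-wide scoring instead of two.

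The effect is limited. Bias can act only through what participants see before scoring. The number of added outcomes, the number of proposers per outcome, proposers' tendency to score high and the resulting shift are all unstated; the first is unknown and the others are assumptions here. The consequence is confined to added outcomes, and the consensus meeting may soften it, although a meeting vote is not an anonymous re-score. The validity of the core outcome set as a whole is not in question. A change is worth making because the rule is explicit and the correction is cheap.

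**What to change.** Add two rules to the Delphi survey methods.

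1. **Display.** In round two, flag outcomes added in round one as new and show them without any group score feedback.
2. **Classification.** Because they have been scored once, do not treat their Table 1 class as final, whether 'in' or 'out'. Take them all to the consensus meeting marked 'scored once', with their round-two distribution by stakeholder group. Applying this in both directions matters: accepting a one-off 'in' while questioning a one-off 'out' would leave half the problem in place.

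The cost is a survey display setting, a short addition to the text and a few more items at the consensus meeting. The Trial status section reports recruitment complete by 14/6/2018. If round two has already run, the display rule can no longer be applied, but the second rule still can be, together with a statement of what feedback participants saw for added outcomes.
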